**Fig. 1 Fig1:**
[figure not shown]
Sample size calculation—output from Open Epi

### Recruitment {15}

Patients regularly attending diabetes clinics in PAT are invited to participate if meeting the eligibility criteria. In order to identify the eligible participants, clinicians will use the list of patients with a scheduled appointment at the clinics (either face-to-face or online) and then check their medical history through the HIS database. Recruitment will stop when the targeted sample size is reached. Enquires (by phone or by email) from the potential participants are answered by the staff of the clinics during business hours.

## Assignment of interventions: allocation and blinding

### Sequence generation {16a}

Stratification is applied by centre (Rovereto and Trento). Participants are randomised (block randomisation with block size of 10) to either the intervention or control group on a 1:1 basis.

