### Trial design {8}

The Telemechron study was designed as a multi-centre, open-label, randomised, superiority study with two parallel groups and a 1:1 allocation ratio. This study design was chosen over others because RCTs are considered the best type of study design to evaluate the effectiveness of health interventions [19].

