### Eligibility criteria {10}

Participants must meet at randomisation all the inclusion criteria and none of the exclusion criteria listed in Table 1.

**Table 1 Tab1:** Inclusion and exclusion criteria

Inclusion criteria	Exclusion criteria
• Being diagnosed with T2DM; • Aged ≥ 18 and ≤ 85 years old; • Having an HbA1c level > 7% (53 mmol/mol) and < 12% (108 mmol/mol); • Being able to walk without walking aids; • Having provided written informed consent; • Having a smartphone or a tablet and being able to download the App that will be used to insert the required data	• Having a BMI < 18 kg/m^2^ and > 45 kg/m^2^; • Having a sBP < 100 or > 200 mmHg and/or dBP < 50 or > 120 mmHg; • Being diagnosed with a stage 5 CKD^a^ • Being diagnosed with a NYHA stage IV; • Poor collaboration (i.e. unwilling to modify the actual plan of control and therapy, even if not ideal) for which adherence to the study is unlikely • Having no possibility of using a smartphone or a tablet • Having medical conditions affecting the study participation (i.e. life expectancy < 1 year)

*Abbreviations*: *BMI* body mass index, *CKD* chronic kidney disease, *dBP* diastolic BP, *HbA1c* glycated haemoglobin type A1c, *NYHA* New York Heart Association, *T2DM* type 2 diabetes mellitus, *sBP* systolic BP

^a^based on the glomerular filtration rate according to the CKD-Epidemiology Collaboration equation < 15 ml/min/m^2^ accounting for individual body surface [20]

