Clinicians will then prescribe the App for a 12-month period through the online medical dashboard. The dashboard allows the visualisation of the information shared by the participant. Moreover, it enables healthcare staff to interact directly through video-chat and chat with the participant. A menu allows clinicians to set up a specific and personalised plan for each participant: they are asked to indicate which parameter (e.g. BP) should be registered in the App and to activate reminders at set intervals. During the 12-month follow-up, clinicians will regularly check the information entered by the participant (minimum frequency of 45 days). Clinicians can provide advice based on the information shared by the participant (e.g. inviting the participant to book an appointment with their general practitioner—GP). Participants will receive the training for the use of the App as soon as they are allocated to the intervention group. A member of the research team (registered nurse) will show the participant how the App works, highlighting its different features. The appointed person will specifically show how to enter the PIN when asked, insert different types of data in the App, write in the chat, and fill in the questionnaire. Also, the registered nurse could be contacted by phone in case of problems managing the app. The app’s chat was another way to contact researchers and IT personnel to solve management problems. Paper-based training material can be provided to the participant upon request.

Table 2 depicts the App features (for the prescriber and the participant perspectives) and provides an explanation of their use.

**Table 2 Tab2:** TreC Diabete App features and related description

Level	Feature	Description
Dashboard (prescriber)	Activation of credentials for the participant	The feature allows to activate the App for a specific participant and is performed by the clinicians via dashboard
Dashboard (prescriber)	Setup of the data each participant will be required to enter into the App	The feature allows the clinician to decide which data the participant will be asked to enter by the App. It allows the storage of the data and the sharing of information
Dashboard (prescriber)	Display of data	The feature allows the user to view the data as entered by the participant. It allows the sharing of the information, which cannot be altered or modified

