### Implementation {16c}

All patients who give consent for participation and who fulfil the inclusion criteria will be randomised.

The random allocation sequence was generated by one statistician from the Clinical and Evaluation Epidemiology Unit of the Local Health Trust (APSS of the PAT), not involved with the recruitment and enrolment of the participants. The statistician used a SAS macro applying blocks following stratification by centre of recruitment. In every centre, closed opaque envelopes with printed randomisation numbers on it are available. For every randomisation number, the corresponding code for the parallel groups of the randomisation list will be found inside the envelopes.

A dedicated member of the research team will open the envelope and will find the allocated group for the participant. Then, the same member of the research team will give the information about group allocation to the patient.

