### Who will be blinded {17a}

Given the nature of the intervention, which is the active use of the Smartphone App, it will not be possible to guarantee the blindness of participants, healthcare staff and the person responsible for data collection. Vital signs, body weight and height are recorded before randomisation by a trained nurse across sites, using standardised procedures and instruments. The blood tests’ analysis will be carried out within the Trusts according to standardised procedures. Laboratory personnel are not involved in the study, thus they are not aware of the participants’ allocation. Blindness is guaranteed during data analysis, as data analysis will be performed from assessors that are not directly involved in the study. Filled-in questionnaires will only report the unique randomisation number.

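### One constant block size of 10 in each centre of an open-label trial, not stated to be withheld from site staff, can make some late-block assignments deducible despite opaque envelopes

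*Protocol article*

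**What the plan says.** Sequence generation {16a} stratifies by centre (Rovereto and Trento) and fixes one block size: "Participants are randomised (block randomisation with block size of 10) to either the intervention or control group on a 1:1 basis". No variation in size is described, and nothing says that the size is concealed from the clinics.

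Trial design {8} describes a "multi-centre, open-label, randomised, superiority study with two parallel groups and a 1:1 allocation ratio". Who will be blinded {17a} concedes that "it will not be possible to guarantee the blindness of participants, healthcare staff and the person responsible for data collection".

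Past assignments are visible to the people who recruit:
- Intervention description {11a}: "Clinicians will then prescribe the App for a 12-month period through the online medical dashboard".
- Implementation {16c}: "A dedicated member of the research team will open the envelope", and the same person tells the patient the arm.
- Recruitment {15}: "In order to identify the eligible participants, clinicians will use the list of patients with a scheduled appointment at the clinics".
- Eligibility criteria {10}, Table 1, excludes patients judged to collaborate poorly, "for which adherence to the study is unlikely". The criteria have to be met at randomisation.

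There are real safeguards. Under Concealment mechanism {16b} and Implementation {16c}, a statistician outside recruitment made the list. The envelopes are opaque and are opened only after consent and baseline collection. Every consenting patient who fulfils the inclusion criteria is to be randomised.

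**The concern.** An opaque envelope stops anyone reading the next card. It does not stop the card being deduced. In a 5:5 block, once five of either arm have appeared, the rest of the block is known to anyone who knows the block length and has kept count. Here every earlier assignment at a centre is visible to clinic and research staff, and those staff also decide whom to approach, when, and whether the patient is collaborative enough to enter.

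A clinician who knows that the next assignment is the App could bring forward a motivated patient, or hold one back when control is due. Motivation and willingness to change therapy plausibly affect 12-month HbA1c, so the comparison would lean towards the App. Measuring HbA1c in a laboratory unaware of allocation does not help, because selection changes who enters each arm. The comparison named in Analysis primary and secondary endpoints {20a} is a t test or rank-sum test, with no baseline adjustment mentioned.

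**Working it through.** **Inputs from the article.** Block size 10 at 1:1, so 5:5, by centre ({16a}). Planned sample 120, planned means 49 and 52 mmol/mol, difference 3 ({14}). Screening 7 to 21 days and consent 7 to 14 days before T0, allocation at 0 months (Table 4). Registration on 29 November 2022, before inclusion began (abstract). Recruitment planned to be complete by April 2023 (Trial status).

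**Assumptions not in the article.** Staff know or infer the size 10 and keep a tally. They steer only when certain, choosing a patient whose expected 12-month HbA1c is d mmol/mol lower when the App is due and d higher when control is due. The range d = 1 to 3 is illustrative.

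**Step 1: assignments certain in advance.** The probability that at least the last k assignments of a 5:5 block are determined is 2 × C(10−k, 5) / C(10, 5), with C(10, 5) = 252:
- k = 1: 2 × 126/252 = 1.000
- k = 2: 2 × 56/252 = 0.444
- k = 3: 2 × 21/252 = 0.167
- k = 4: 2 × 6/252 = 0.048
- k = 5: 2 × 1/252 = 0.008

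The sum is 1.667 per block, or 16.7%. Over 120/10 = 12 complete blocks that is 12 × 1.667 = 20 assignments. A fixed block of 4 would give 33.3%, so 10 is already better than a small fixed block.

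**Step 2: upper bound on bias.** On average half of the 1.667 certain places fall in each arm of five. The App mean shifts by −(0.833/5)d and the control mean by +(0.833/5)d. The arm difference shifts by 1.667d/5 = 0.33d, which is 0.33 mmol/mol for d = 1 and 1.0 for d = 3. Steered App and control patients then differ by 2d, that is 2 to 6 mmol/mol, which is a strong degree of steering.

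**Step 3: effect of the interval between choosing and allocating.** If L other allocations occur at the centre between fixing the candidate and opening the envelope, only the terms k ≥ L+1 of Step 1 count:

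| L | certain per block | % certain | bias |
|---|---|---|---|
| 0 | 1.667 | 16.7 | 0.33d |
| 1 | 0.667 | 6.7 | 0.13d |
| 2 | 0.222 | 2.2 | 0.04d |
| 3 | 0.056 | 0.6 | 0.01d |
| 5 | 0 | 0 | 0 |

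From registration to the end of April 2023 is about 22 weeks. Assuming an even pace and equal centres, 120/22/2 is about 2.7 allocations per centre per week, so roughly 3 to 5 fall within 7 to 14 days.

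**Step 4: what varied blocks change.** In simulation (60 patients per centre assumed), sizes drawn at random from 6, 8 and 10 reduce the certain share from 16.7% to below 2%, even for a guesser who knows the set of sizes. The rate of correct guesses from always choosing the arm with fewer assignments so far hardly moves: 65.3% with a fixed 10, about 66% with 6/8/10, and 65.3% with 6/8/10/12.

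**The case against.** The strongest reply has four parts.

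**Knowledge.** Nothing says that the clinics were told the block size, and an independent statistician made the list. The published article postdates the planned end of recruitment, so on that plan it could not have disclosed the size in time. This stands as a condition on the concern. The article does not say that the size was withheld either.

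**Timing.** With consent 7 to 14 days before allocation and all consenting eligible patients randomised, most of the predictability has gone by the time it could be used (Step 3). This largely stands for the decision to invite. It does not fully close the gap: eligibility has to hold at randomisation, so the collaboration judgement stays open until then, and the article gives no rule for the order in which waiting patients draw envelopes.

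**Best guessing.** A reader might infer a larger bias from the 65.3% best-guess rate: correct minus wrong guesses are 2 × 6.53 − 10 = 3.06 per block, hence 3.06d/5 = 0.61d, or up to 1.8 mmol/mol for d = 3. That should not be charged to the fixed size. The guess needs only a running tally, and varied blocks leave it essentially unchanged (Step 4).

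**Detection.** It would be too strong to say that selection could not be seen. Baseline HbA1c and clinical variables are collected before allocation and MMAS-4 at T0, so imbalance in related characteristics can be inspected, though motivation itself cannot.

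**Conclusion.** The weakness is real but moderate. A constant block size, visible past allocations and recruiter discretion together leave up to 16.7% of assignments (about 20 of 120) deducible, with a bias of at most 0.33d: 0.33 to 1.0 mmol/mol for an assumed d of 1 to 3, against a planned difference of 3. That ceiling needs staff to know or infer the size, to keep count, to act on every certain assignment, and to act with the next envelope as good as in hand. With three intervening allocations the certain share is 0.6% and the bias 0.01d.

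A reader might infer that selection took place or that concealment failed. The article supports neither. It shows an avoidable opening that the envelopes do not fully close.

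**What to change.** **If unopened envelopes remain.** Regenerate the rest of the list with randomly varied block sizes within centre, and withhold the sizes from clinic and research staff. Record and date the eligibility decision, including the collaboration judgement, before the envelope is drawn, and draw envelopes in a fixed order. The cost is one rerun of the existing SAS macro and refilling the unopened envelopes. The small downside is a slightly larger possible imbalance within a centre when recruitment ends. Varied sizes remove nearly all certain predictions but not tally-based guessing, so the dated judgement and the fixed order are needed as well.

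**If recruitment is complete.** Compare baseline HbA1c, other baseline characteristics and screening exclusions by position in block within centre, and add a baseline-adjusted sensitivity analysis of 12-month HbA1c. Report whether site staff knew the block size. The baseline comparisons and the adjusted analysis use data already scheduled in Table 4. The comparison of exclusions needs dated screening records. Adjustment cannot correct for unmeasured motivation.

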### Concealment mechanism {16b}

Treatment assignment information is enclosed in opaque envelopes, which are unsealed once the participant provides the written informed consent and the baseline information is collected.

### Implementation {16c}

All patients who give consent for participation and who fulfil the inclusion criteria will be randomised.

The random allocation sequence was generated by one statistician from the Clinical and Evaluation Epidemiology Unit of the Local Health Trust (APSS of the PAT), not involved with the recruitment and enrolment of the participants. The statistician used a SAS macro applying blocks following stratification by centre of recruitment. In every centre, closed opaque envelopes with printed randomisation numbers on it are available. For every randomisation number, the corresponding code for the parallel groups of the randomisation list will be found inside the envelopes.

A dedicated member of the research team will open the envelope and will find the allocated group for the participant. Then, the same member of the research team will give the information about group allocation to the patient.

### Who will be blinded {17a}

Given the nature of the intervention, which is the active use of the Smartphone App, it will not be possible to guarantee the blindness of participants, healthcare staff and the person responsible for data collection. Vital signs, body weight and height are recorded before randomisation by a trained nurse across sites, using standardised procedures and instruments. The blood tests’ analysis will be carried out within the Trusts according to standardised procedures. Laboratory personnel are not involved in the study, thus they are not aware of the participants’ allocation. Blindness is guaranteed during data analysis, as data analysis will be performed from assessors that are not directly involved in the study. Filled-in questionnaires will only report the unique randomisation number.

### Procedure for unblinding if needed {17b}

This is an open-label trial, in which only data analysts will not be aware of participant allocation. Therefore, unblinding of treatment allocation to the participants or the staff involved in the care of the participants will not be an applicable procedure for this specific trial.

## Data collection and management

### Plans for assessment and collection of outcomes {18a}

The large majority of the data (e.g. demographic data, clinical information) are collected as part of the standard routine practice. Other data are collected through interviews and questionnaires that are provided during different times of the study. Those assigned to the intervention group will be asked to provide information through the App (e-diary and Virtual Coach), whilst those assigned to the control group will register the data as per routine (e.g. paper diary). Please refer to Table 4 under the “Outcomes {12}” section for the information regarding the involvement of personnel—participants and the source of information used for data collection.

Below, a short description of the questionnaires used during this study is provided:Quality of life questionnaire “SF-12”: composed of 12 items (obtained from 36 items of the original SF-36 questionnaire) and providing two measures related to two different aspects of health: physical health and mental health [33, 34].Activity status evaluated through the “Duke Activity Status Index—DASI scale”, which measures the functional capacity perceived by the participant. It is a 12-item scale with a score that ranges from 0 (worst) to 58.2 (best). A difference of 2 or more is considered clinically significant [35, 36].Daily physical activity level, evaluated using the “Physical Activity Questionnaire Daily – IPAQ” questionnaire, composed of 4 generic items with open-ended questions regarding last 7-day recall of physical activity [37];Evaluation of medication adherence using the Morisky Medication Adherence Scale in the 4-item version (MMAS-4) [38]. The scale consists of 4 questions with a score of 0 and 1 for a “Yes” and “No” answer, respectively. The questions are summed to give a range of scores from 0 (high adherence) to 4 (low adherence). The questionnaire answers will be collected during the face-to-face meeting with the research team.App user satisfaction using the System Usability Scale (SUS): The scale consists of 10 questions with a score ranging from 1 (strong disagreement) to 5 (strong agreement). Each score is then multiplied by 2.5, resulting in a total score ranging from 0 to 100. A 68 score is considered above average [39].

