#### Secondary outcome measures

Secondary outcome measures are collected at different time point (for specific times of data collection refer to Table 4).Proportion of participants with Hb1Ac < 53 mmol/mol within the two arms;Difference in HbA1c levels between the two arms other than at 12 months;Reporting frequency and number of new hypoglycaemic episodes within the two arms;Proportion of participants reaching the targeted lipid profile (LDL level < 70 mg/dl and non-HLD cholesterol level < 100 mg/dl) and BP levels (sBP < 130 mmHg or > 140 if ≥ 65 years old);Effect on weight, lipid profile and BP levels for the App users;Effect on physical activity performed during the last 7 days prior filling in the questionnaire, for both arm participants;Number of hospitalisation events within the two arms;Number of measurements and level of physical activity with the prescribed activities (body weight monitoring, BP measurements, physical activity) within the two arms;Changes in quality of life (QoL) scores for participants of both arms;Satisfaction and usability score of the App in the intervention arm;

**Table 4 Tab4:** Time schedule of enrolment, interventions and assessments during the study period, adapted from the example template provided by the SPIRIT Group [28]

	Enrolment		Allocation		Post-allocation			Close-out	Personnel and participant involvement	Method of data collection
Timepoint	14 to 21 days prior T0	7 to 14 days prior T0	0 months	0 months (T0)	3 months (T1) (± 30 days)	6 months (T2) (± 30 days)	9 months (T3) (± 30 days)	12 months (T4) (± 30 days)		
ENROLLMENT										
** Informal study information**	x	x							Clinician	Scheduled appointment at clinic
** Eligibility screen**	x	x							Clinician or PI	Scheduled appointment at clinic
** Informed consent signed**		x							Clinician or PI and participant	Face-to-face meeting
** Allocation**			x						Research team	Face-to-face meeting
** Blood tests prescription**		x							Clinician	Face-to-face meeting
** Provide 3 copies of IPAQ questionnaire**		x							Research team	Face-to-face meeting
INTERVENTION										
** App education and instruction manual**				x					Research team	Face to face meeting
** Inform GP of participation**				x					Clinician	Through email
** Help and support with the App use**				x	x	x	x	x	Research team	Phone- email
** App (intervention) monitoring**				x	x	x	x	x	Clinician or research team	Medical dashboard

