** Medical intervention via App – data recording**				x	x	x	x	x	Clinician and participant	Medical dashboard
ASSESSMENTS: clinical and biohumoral variables and clinical indicators										
** Body weight and number of checks (previous month)**		x			x	x	x	x	Research team	Face to face meeting, medical dashboard /App or other recording tools
** Vital signs and number of checks (previous month)**		x			x	x	x	x	Research team	Face to face meeting, medical dashboard/App or other recording tools
** Demographic characteristics and clinical variables**^**a**^		x							Clinician and research team	Face to face meeting, HIS
** Hb1Ac levels and number of checks**		x			x	x	x	x	Clinician, research team, laboratory personnel	HIS
** Other blood tests**^**b**^		x						x	Clinician, research team, laboratory personnel	HIS
** Questionnaires (SF-12/MMAS-4/DASI)**				x				x	Research team, participant	Face to face meeting
** IPAQ questionnaire**				x	x	x	x	x	Research team, participant	Face to face meeting and phone call
** SUS questionnaire (App group only)**								x	Research team, participant	Face-to-face meeting
** Number of nursing and medical (tele)consultation and chat interactions**					x	x	x	x	Research team	Medical dashboard/App and HIS
** Number of unscheduled specialists visits (macro- and micro-vascular complications), number of accesses to ED for cardiac, cardiovascular or diabetic problems**					x	x	x	x	Research team	HIS
** Number of therapeutic plan changes**					x	x	x	x	Research team	Medical dashboard/App and HIS
** Time spent for (tele)consultation**						x			Research team	Recording of time during visit
** Number of hospitalisation**						x	x	x	Research team	HIS
** Number of hypoglycaemic episodes**					x	x	x	x	Research team, participants	Medical dashboard/App and/or download of data from glucometer

*Abbreviations*: *DASI* Duke Activity Status Index, *ED* emergency department, *HbA1c* Glycosylated Haemoglobin Type A1C, *HIS* Hospital Information System, *IPAQ* International Physical Activity Questionnaire, *MMSA-4* Morisky Medication Adherence Scale, *SF-12* Short Form-12, *SUS* System Usability Scale, *PI* Principal Investigator

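### The stated SUS scoring rule gives totals of 25 to 125, not the stated 0 to 100, so a total scored literally is not on the scale of the quoted reference value of 68

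*Protocol article*

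**What the plan says.** The scoring is set out in the protocol article under Plans for assessment and collection of outcomes {18a}, in the last entry of the questionnaire list. The items are described as follows: "The scale consists of 10 questions with a score ranging from 1 (strong disagreement) to 5 (strong agreement"). The next sentence gives the conversion: "Each score is then multiplied by 2.5, resulting in a total score ranging from 0 to 100". The last gives a reference value: "A 68 score is considered above average".

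The measure is a listed secondary outcome: "Satisfaction and usability score of the App in the intervention arm" (Secondary outcome measures). Table 4 schedules it once, at 12 months, for the App group only. No recoding of the item answers is described there or elsewhere in the article.

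**The concern.** The item range, the multiplier and the total range stand in consecutive sentences and cannot all be true. No item can score below 1, so a total of 0 is impossible, and the highest answers go well past 100.

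The scale matters because the score has no control-arm comparison. The only yardstick the article offers for reading it is 68, and that value is given alongside a 0 to 100 scale. If whoever scores the questionnaires follows the sentence as written, the totals are on a different scale and setting them beside 68 means nothing. Totals above 100 would be noticed. Literal totals between 25 and 100 would look plausible and could pass unremarked.

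**Working it through.** **Inputs**, all from Plans for assessment and collection of outcomes {18a}: 10 items; item answers 1 to 5, midpoint 3; multiplier 2.5; stated total range 0 to 100; reference value 68.

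**1. Attempt to reproduce the stated range.** Total = sum over the ten items of (2.5 × item score).

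- Minimum: 10 × 1 × 2.5 = 25
- Maximum: 10 × 5 × 2.5 = 125
- All neutral: 10 × 3 × 2.5 = 75

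The stated 0 to 100 is not reproduced.

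**2. Other readings of the sentence.**

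| Reading | Minimum | Maximum |
|---|---|---|
| 2.5 × mean item score | 2.5 | 12.5 |
| Sum with no multiplier | 10 | 50 |
| Multiplier 2 in place of 2.5 | 20 | 100 |
| Items recoded to 0–4, then × 2.5 | 0 | 100 |

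Of these, only the last gives 0 to 100. The stated figures point to it as well: 100 / (10 × 2.5) = 4 points per item, starting from 0. On that scale an all-neutral respondent scores 10 × 2 × 2.5 = 50.

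**3. Position relative to 68, if no item is reverse-scored.** The mean raw answer needed to reach 68 is:

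- Literal rule: 68 / (10 × 2.5) = 2.72, which is below neutral
- Recoded items: 68 / (10 × 2.5) + 1 = 3.72

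**4. Size of the error if some items are reverse-scored.** The article does not give item direction, so let k be the number of reversed items, N their raw sum and P the raw sum of the other 10 − k items.

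- Literal total = 2.5 × (P + N)
- Recoded total = 2.5 × [(P − (10 − k)) + (5k − N)]
- Literal minus recoded = 2.5 × (2N + 10 − 6k)

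With numbers put in:

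- k = 0: 2.5 × 10 = +25 for everyone
- k = 1, N from 1 to 5: 2.5 × 6 = +15 to 2.5 × 14 = +35
- k = 5 (an illustrative assumption), N from 5 to 25: 2.5 × (−10) = −25 to 2.5 × 30 = +75
- All neutral, any k: N = 3k, so 2.5 × (6k + 10 − 6k) = +25, that is 75 against 50

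With k = 5, a respondent giving the most favourable answer to every item would score 2.5 × (5 × 5 + 5 × 1) = 75 literally, against 100 when recoded. The literal rule would then understate usability. The all-neutral example is the same whatever k is; the error for other patterns is not.

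**The case against.** The best defence is that this is a wording slip in a condensed article. The questionnaire list is introduced as a brief description, a source is cited for the instrument, and item-level scoring is commonly left to the full protocol, the analysis plan or the instrument itself. The stated 0 to 100 range suggests that the intended scoring is right and that a step dropped out of the text. The score is collected once, in one arm, and if the raw answers are kept any slip can be put right later.

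Most of this stands, and it limits the consequence. It does not remove the point. The article does not stay silent on the scoring. It states a rule, and that rule contradicts the range in the same sentence. The range and consistency checks under Data transmission and editing are described for data entry. Item answers of 1 to 5 would pass such checks, so they would not necessarily expose a wrong total.

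A reader might infer something stronger: that every total will be 25 points too high and that the App will therefore look above 68 by construction. The documents do not support that, for four reasons.

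- The constant +25 holds only if no item is reverse-scored, and the article gives no item direction. With reversed items the error varies and can be negative.
- Even with no reversal, not every pattern clears 68: a mean item answer of 2.5 gives 10 × 2.5 × 2.5 = 62.5.
- The value 68 is an interpretive remark. No success criterion, test or decision rule in the article uses it.
- Any distortion arises only if the sentence is applied literally, and nothing shows that it will be.

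**Conclusion.** The point holds as an internal contradiction in a stated scoring rule. Items scored 1 to 5 and multiplied by 2.5 give 25 to 125, and the stated 0 to 100 cannot come from them. A literal total is not comparable with 68. The all-neutral respondent shows how much can turn on it: 75 against 50, a difference of 25 points across the reference value, whatever the item direction. For other answer patterns neither the size nor the direction of the error can be fixed from the document.

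The contradiction itself needs no assumption beyond the figures printed in the article. A practical effect on results further requires that the literal rule be used. It would touch one secondary outcome, measured in the App arm only. The HbA1c comparison and the sample size are unaffected. This is a minor correction.

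**What to change.** Replace the conversion sentence with a rule that matches its range: recode each of the ten items to a 0 to 4 contribution following the instrument's own scoring (including any reversed items), sum the ten contributions, and multiply the sum by 2.5 to give 0 to 100. Refer to 68 only for scores obtained in that way. Before the 12-month questionnaires are scored, check that the scoring program follows the same rule, and keep the raw item answers so that totals can be recomputed.

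The cost is one sentence and a check of the scoring code. No new data are needed.
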